Hester *et al.*, 2023) and, collectively, professionals feel that they could be more effective. Furthermore, recent evidence suggests that COVID-19 has had a huge impact on the CJS, creating a backlog within an already pressurised process. Extreme delays within the CJS can only exacerbate the issues already present prior to the pandemic.

One innovative approach to diversion from the CJS pathway, “Project CARA”, was developed in 2011, as a conditional caution offered by the police to first time adult offenders of DVA of standard risk according to the DASH domestic abuse checklist and professional judgement. This initiative provided an alternative beyond a ‘simple caution’ or ‘no further action.’ A caution requires the offender to admit culpability in order to be an available disposal option. Hampshire Constabulary in England were ambitious to test an alternative response via an early intervention that would improve outcomes for victim-survivors and their families. Under this model, offenders are required to undertake two mandatory workshops that increase awareness of their abusive behaviour and the safety of partners and children. If, however, they fail to comply with the conditions of this caution, they may be prosecuted for the original offence. In contrast to restorative justice, CARA is an awareness raising intervention for offenders, that utilises a trauma-informed approach and motivational interviewing techniques. In these workshops, offenders are further signposted onto services that support improvements in the wider determinants of their offending behaviour, such as to primary care, drug and alcohol services or onto a community perpetrator programme. Project CARA itself rests on several assumptions about DVA and health inequalities. First, drawing on Marmot
*et al.*, Project CARA recognises the potential lifelong impacts of DVA on health, social and economic outcomes throughout the life-course and aims to tackle the multiplicity of disadvantage and the impact that this can have upon health. Project CARA stresses the importance of early intervention and an understanding that health must not be viewed in isolation, both of which are at the heart of local Health and Wellbeing Board strategies (
Myhill & Bartlett, 2024). An initial experimental trial of CARA was undertaken in Southampton custody suite, showing a reduction in the frequency of re-arrest and prevalence of domestic abuse in the intervention arm, one year following allocation (

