## Aims and objectives

Using a pragmatic concurrent mixed methods design the aim of our study is to evaluate Project CARA following its wider rollout nationally. By using this approach to mixed method study design, both methods will be conducted and analysed independently before findings are later integrated together (
Creswell & Plano Clark, 2018).

Our research objectives are to:

Understand the perceptions and experiences of clients, partners/former partners and professionals involved in the delivery of Project CARA.Examine whether the completion of the CARA conditional caution leads to a reduction in the incidence and/or severity of DVA at the population level.Develop an overarching logic model for Project CARA in order to understand the mechanisms of action of intervention components and anticipated outcomes (all phases).Explore the wider contextual factors around offending behaviour and answer research questions around the implementation of CARA including, for example, the types of violence that result in a CARA caution.Analyse the cost-benefits of Project CARA in comparison with a matched cohort who do not receive Project CARA.

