**Figure 1. f1:**
[figure not shown]
Hypothesis 1: Completion of the CARA conditional caution leads to a reduction in incidence and/or severity of DVA at the population level.

**
*Data source*
**: Data held on the police Record Management System (RMS) database, or equivalent, will be extracted, pseudonymised and shared in aggregated form.

**
*Population*
**: The population sample to be included in the analysis are those that are eligible for the CARA intervention.

**
*Intervention*
**: Those who have undertaken the CARA intervention will form the intervention group. CARA is a conditional diversionary caution offered by the police to first time adult offenders of DVA of standard risk or medium risk (in some areas). Offenders are required to undertake two mandatory workshops that increase awareness of their abusive behaviour and the safety of partners and children. In contrast to restorative justice, CARA is an awareness raising intervention for offenders, that utilises a trauma informed approach and motivational interviewing techniques across the pair of workshops. In these workshops offenders are further signposted onto services that support improvements in the wider determinants of their offending behaviour, such as to their GP, drug and alcohol services or onto a community perpetrator programme.

**
*Comparison*
**: Using PSM approaches a comparator group will be formed from those who meet the eligibility criteria for CARA but are based in an area that is currently not delivering the CARA intervention. Covariates for the matching will include demographics, such as age, gender, ethnicity, whether in same sex relationship; offending behaviour/wider determinants, such as offending history and/or risk profile, mental health, employment status, alcohol misuse, accommodation type and; wider contextual factors, such engagement with other perpetrator interventions.

**
*Outcome measures*
**: The primary outcome will be DVA
reoffending within 12 months. The primary outcome will be described as either i) number of DVA arrests ii) number of DVA crimes. The secondary outcome(s) will include for example total number of arrests, crime severity score, total number of offences.

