### Analysis of quantitative data

**
*Interrupted time series*
**. Using interrupted time series (ITS), we will also examine whether the introduction of the CARA conditional caution leads to a hypothesised population-based reduction in the incidence of DVA, as hypothesised in Figure 2. A secondary outcome will be to assess if there was a change in the severity of recorded DVA before and after the introduction of CARA.

 As an intervention study design, ITS is a valuable study design compared to traditional observational study designs (such as cohort or case control studies) particularly when there is a need for retrospective evaluations which have already been implemented, either without randomization or to a whole population, both of which are applicable in the CARA intervention (
Bernal *et al.*, 2017). By nature, ITS can be applied to natural experiments when an intervention is introduced at the population level at a clearly defined period of time and involves observing a single population over time.

In an ITS study, a time series of the outcome of interest (incidence of domestic violence and abuse) is used to establish an underlying trend, which is ‘interrupted’ by an intervention (e.g. CARA being offered in a force area) at a known point in time. The pre-intervention underlying trend is compared with the post-intervention period to identify whether the intervention is associated with any changes in outcome.

Initially summary statistics and plots will be undertaken, including a scatter plot of the time series demonstrating before and after comparisons of the incidence of DVA across the force areas. These will include sub-analyses, by age, gender, ethnicity, force area and whether in same sex relationship.

Following this a segmented regression model such as the one below will be constructed to undertake the ITS model:

Yt-=α+β1Tt+β2Xt+β3XtTt

Yt is the aggregated outcome variable measured at each equally-spaced time point (month)

Tt is time

Xt is study phase

XtTt is time after interruption

α, β1, β2 and β3 are model parameters

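### In the matched cohort, the CARA arm is defined by having undertaken the workshops and the comparators by eligibility alone, so CARA can look effective with no effect

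*Protocol article*

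**What the plan says.** The protocol article, under Population, intervention, comparison and outcome, takes as its population people eligible for CARA and then defines the two arms differently.

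- **Intervention:** "Those who have undertaken the CARA intervention will form the intervention group". The same paragraph adds: "Offenders are required to undertake two mandatory workshops".
- **Comparison:** by propensity score matching, "a comparator group will be formed from those who meet the eligibility criteria for CARA but are based in an area" where CARA is not being delivered. The matching covariates are demographics, offending history and/or risk profile, mental health, employment, alcohol misuse, accommodation and contact with other perpetrator interventions.
- **Outcome measures:** the primary outcome is DVA reoffending within 12 months, described as a number of arrests or of crimes.

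Hypothesis 1, in the caption of Figure 1, reads: "Completion of the CARA conditional caution leads to a reduction in incidence and/or severity of DVA at the population level". Objective 2 in Aims and objectives uses the same exposure: "Examine whether the completion of the CARA conditional caution leads to a reduction in the incidence and/or severity of DVA at the population level". The interrupted time series has a different one: "whether the introduction of the CARA conditional caution leads to a hypothesised population-based reduction in the incidence of DVA".

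The Introduction makes clear that some offenders will not comply: "If, however, they fail to comply with the conditions of this caution, they may be prosecuted for the original offence". It also says that a caution is available only to someone who admits culpability.

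**The concern.** One arm is defined by what a person did after disposal, the other by status at baseline. An offender who is issued the caution and does not attend, or who breaches it and is prosecuted, falls out of the CARA arm. The same kind of person in a non-delivering area remains available as a comparator. If compliers would reoffend less anyway, the CARA arm has been selected for low risk.

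Matching cannot fully repair this. No listed covariate measures compliance with a caution, and nobody in a non-delivering area was offered CARA, so compliance cannot be observed there. A larger national sample does not help either: it narrows the interval around the same biased value.

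The affected result is the individual-level primary outcome, and through it the cost per reoffence avoided, which is also built on matched controls. The Dissemination plan expects the findings to inform commissioning and possibly legislation. Police can decide whether to issue a CARA caution; they cannot assign completion. The effect of issuing or introducing CARA is therefore the one those readers need.

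The wording of objective 2 and Hypothesis 1 adds to the difficulty. It attributes a population-level effect to completion, whereas the time series examines introduction and the cohort examines individuals. It fits neither analysis.

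**Working it through.** The article gives no completion rate, reoffending rate or time to completion, so there is no figure of its own to reproduce. All inputs below are assumptions, and the true effect of CARA is set to nil throughout.

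**1. Selection of compliers.** Let c be the share completing, pc the 12-month reoffending risk in completers and pn the risk in non-completers. With no effect, an eligible comparator group has the same mix of would-be compliers and non-compliers, so

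apparent risk ratio = pc / (c × pc + (1 − c) × pn).

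Assumed ranges: c = 0.7-0.9, pc = 0.20-0.25, pn = 0.35-0.45.

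| c | pc | pn | Comparator risk | Apparent RR |
|---|---|---|---|---|
| 0.7 | 0.20 | 0.45 | 0.140 + 0.135 = 0.275 | 0.73 (lowest) |
| 0.7 | 0.25 | 0.45 | 0.175 + 0.135 = 0.310 | 0.81 |
| 0.8 | 0.25 | 0.45 | 0.200 + 0.090 = 0.290 | 0.86 |
| 0.9 | 0.25 | 0.45 | 0.225 + 0.045 = 0.270 | 0.93 |
| 0.9 | 0.25 | 0.35 | 0.225 + 0.035 = 0.260 | 0.96 (highest) |

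The ratio is 1.00 if everyone completes (c = 1) or if completers and non-completers carry the same risk (pc = pn). The calculation gives no credit for matching. It uses a binary risk, whereas the primary outcome is a count; because the formula is a ratio of averages, it applies equally to mean counts.

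**2. Immortal time, only under a further condition.** Suppose the clock starts at disposal in both arms and anyone who reoffends before completing is excluded from the CARA arm. With 12-month risk p, constant hazard h = −ln(1 − p)/12 and m months to completion,

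apparent risk ratio = [1 − exp(−h(12 − m))] / p.

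For p = 0.20, h = 0.2231/12 = 0.0186 per month:

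- m = 1: 0.185/0.20 = 0.93
- m = 2: 0.170/0.20 = 0.85
- m = 3: 0.154/0.20 = 0.77

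At p = 0.30 the values are 0.93, 0.86 and 0.78.

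If the CARA clock starts at completion instead, the ratio is 1.00 under a constant hazard. Under a falling hazard (Weibull shape 0.7, p = 0.20) it is 0.89, 0.84 and 0.81 for 1, 2 and 3 months.

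Someone who reoffends before completing is already a non-completer in step 1. The two mechanisms overlap, and their effects must not be added or multiplied.

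**3. After the change.** If both arms are defined at baseline and share a time zero, then c = 1 and m = 0 in these formulas. The null ratio returns to 1.00, apart from residual confounding by area.

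**The case against.** Several points on the other side have force.

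- **Comparators are not everyone who is eligible.** A reader might infer that they are, but the plan matches them on risk profile, alcohol misuse, employment and similar factors. These plausibly predict both compliance and reoffending, so matching may absorb part of the selection. It cannot absorb the unmeasured part.
- **'Undertaken' need not mean 'completed'.** The intervention paragraph describes CARA as a caution offered by police, so accepting it is a possible reading. Completion appears only in objective 2 and Hypothesis 1, both worded at population level, whereas the matched cohort concerns individuals. A completers-only arm is the natural reading, given the two mandatory workshops, but not a certain one.
- **Immortal time is not established.** The article states neither when the 12 months begin nor that an early reoffender leaves the CARA arm. A condensed article may leave time zero to the full plan, so its absence is no fault in itself.
- **The question of offering CARA is partly covered.** The time series and, where possible, its controlled version take CARA being offered in a force area as the exposure, whoever completes. They do not share this problem.

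These points limit the size and reach of the concern. They do not remove it: the arms are still defined at different stages, non-compliers are acknowledged, and nothing described in the article puts them back into the CARA arm.

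**Conclusion.** The point holds for the matched cohort and for the cost analysis that relies on it. As written, the arm definitions can produce an apparent benefit from an intervention with no effect. This is a flaw in a stated rule, not missing detail.

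Under the assumed inputs, and before any credit for matching, selection alone gives a risk ratio of 0.73-0.96. Immortal time would give about 0.93-0.77 for 1-3 months to completion, but only if the clock starts at disposal and early reoffenders are excluded; it is not a separate bias to add on top. The real size cannot be derived from the article.

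A reader might go further and conclude that the study will show a false benefit, or that all its quantitative results are compromised. The article does not support either: the bias depends on unknown completion and risk differences, matching may reduce it, and the time series is unaffected.

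**What to change.** 1. Define the CARA arm as all eligible offenders issued a CARA conditional caution, whether or not they attended, and start the 12-month clock at the disposal date in both arms. This also settles the meaning of 'undertaken'.
2. Report beside it, as a main analysis and not only a sensitivity analysis, all recorded-eligible offenders in delivering areas against all recorded-eligible offenders in non-delivering areas. Issue itself depends on admitted culpability and professional judgement, so issued against eligible keeps part of the imbalance.
3. Keep completers as a clearly labelled secondary analysis. Do not use issue as an instrument for completion: issue is not as good as random, and the threat of prosecution could itself affect reoffending.
4. Base the cost analysis on the redefined arms.
5. Reword objective 2 and Hypothesis 1 from completion to issue at the individual level and introduction at the population level.

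The cost is a smaller, diluted effect estimate. Non-completers must also be included in the police extract; since the data are to be shared in aggregated form, this has to be specified before extraction. The all-eligible comparison further needs eligibility to be recorded in both kinds of area.

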**Methods:**

Using a concurrent pragmatic mixed methods design model we will undertake a national evaluation of CARA by triangulating quantitative data from up to nine police forces, and routine data from service providers, with qualitative data from workshop participants, victims and professional stakeholders to: (1) understand the long-term impact of CARA implementation on DVA reoffending and engagement with services and (2) explore perceptions and experiences of both delivery and receipt of CARA. We will use qualitative methodologies that draw on interpretivist and phenomenological perspectives, as well as quantitative methodologies using interrupted time series models, Poisson regression models, Geo mapping and a cost benefits analysis.

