Strang *et al.*, 2017). No further evaluation has been conducted, and both national and qualitative evidence is lacking. Overall the literature is lacking in qualitative evidence around what works for perpetrators, including how to engage them in such interventions, and whether engagement leads to self-awareness and behavioural change. Despite this, CARA has been rolled out nationally and is likely to remain the main-stay intervention for eligible individuals.

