## Qualitative study

### Sampling and recruitment strategy

The qualitative study will involve the recruitment of three different population groups:

Phase One: CARA workshop attendees or others, in matters when a simple caution/no further action was the disposal option (referred to collectively as ‘clients’). Where possible, the inclusion criteria for CARA will be used to ensure that participants are broadly comparable.Phase Two: The partner/ex-partner of clients (referred to as ‘victim-survivors’)Phase Three: Professionals and stakeholders comprising CARA facilitators, police staff, and third sector organisations (referred to as 'stakeholders'). It is anticipated that participants will span organisational structures, operational and strategic level roles

In phase 1 and 2, participants will be purposively sampled according to geographical location, socio-economic status, ethnicity, and CARA participation status. Whilst we will aim for gender diversity within our sample, we have not defined this as a primary sampling variable in recognition of the gendered nature of DVA.

Sample size will be guided by the breadth and focus of the research question(s), the demands placed on participants, the depth of data likely to be generated, and the analytic goals and purpose of the overall project. Following recommendations for pragmatic assumptions around sample size (
Braun & Clarke, 2019), it is anticipated that up to 15 clients, 15 victim-survivors and 15 stakeholders will be interviewed.

**
*Phase one*
**. Participants will be recruited from two separate cohorts: (1) a cohort recruited from those involved with or accessing Project CARA workshops, “CARA workshop attendees
*”* within a participating police force area and (2), a cohort of broadly comparable participants without a Project CARA disposal option in a non-CARA participating area. It is anticipated that CARA workshop attendees will be recruited primarily through the [agency] who have responsibility for the design and delivery of Project CARA workshops within the following participating police force areas: Avon & Somerset, Cambridgeshire, Dorset, Hampshire, Leicestershire, Norfolk, Thames Valley, West Midlands, and West Yorkshire. All participants from non-CARA participating areas will be recruited with the support of police staff and third sector organisations who will act as gatekeepers for the study.

**
*Phase two*

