As our outcome measure (DVA occurrences) are count data, we will also undertake a Poisson model. Calendar quarters will be included as a categorical variable to account for seasonality. The final model will provide a measure of relative risk with 95% confidence intervals to describe the change in incidence in DVA across the CARA sites before and after the introduction of the intervention. We will account for covariates of interest in the final model to examine any changes specific to offender subgroups of interest, including age, sex, ethnicity and socioeconomic status. Confounding events or co-interventions that will affect study outcome will be explored through consultation with the research team, including all stakeholders, and through the qualitative research. Time varying confounders might include, for example, lockdowns from the COVID-19 pandemic.

Where possible we will also aim to undertake a controlled interrupted time series (CITS) (
Bernal *et al.*, 2018). In this case the control data will be derived from sites where CARA was not delivered during the study timeframe. The CITS model can be described as:

Yt-=α+β1Tt+β2Xt+β3XtTt+β4Zt+β5ZtTt+β6ZtXt+β7ZtXtTt

Yt is the aggregated outcome variable measured at each equally-spaced time point (month)

Tt is time

Xt is study phase

XtTt is time after interruption

Zt is treatment or control group

ZtTt is time for treatment and 0 for control,

ZtXt is study phase for treatment and 0 for control,

ZtXtTt is time after interruption for treatment and 0 for control

α, β1, β2 , β3 β4, β5, β6 and β7 are model parameters

**
*Geomapping*
**. We will also undertake geomapping using postcode data from regional and national data (either from the address where the incident took place or the perpetrator’s address). The postcode data will be input using googlemaps to generate a visual-coloured map. The visuals produced through this method are not accurate enough to render an individual’s home address to become identifiable; postcodes are replaced with colour patches, similar to heat maps, covering a large area. The postcodes entered into google through this process are not stored by google and therefore no data will be stored and shared through this method.

**
*Health economics analysis*

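### In the matched cohort CARA is fully determined by police force, so matching on offender characteristics cannot separate a CARA effect from differences in arrest and recording practice

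*Protocol article*

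**What the plan says.** The Protocol article, under Population, intervention, comparison and outcome, fixes both groups of the matched cohort. For the treated: "Those who have undertaken the CARA intervention will form the intervention group". Comparators are offenders who meet the CARA eligibility criteria but are "based in an area that is currently not delivering the CARA intervention". The covariates named for matching are demographics, offending history or risk profile, mental health, employment, alcohol misuse and accommodation. There is also a contextual category, whose one example is engagement with other perpetrator programmes. The primary outcome is DVA reoffending within 12 months, counted as DVA arrests or DVA crimes.

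Under Analysis of quantitative data, the controlled interrupted time series, planned only if feasible, uses another definition of control: "the control data will be derived from sites where CARA was not delivered during the study timeframe".

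On data sources, the abstract's Methods speak of "triangulating quantitative data from up to nine police forces". Sampling and recruitment strategy, in the qualitative part, refers to the agency "who have responsibility for the design and delivery of Project CARA workshops" and lists nine force areas. The Introduction adds: "Despite this, CARA has been rolled out nationally".

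**The concern.** Propensity matching can balance characteristics that vary within both groups. Here the police force does not: one set of forces supplies all the treated and another supplies all the comparators. Arrest policy, charging practice and crime recording belong to the force, and they generate the outcome. Any difference between the two sets of forces therefore passes into the estimated effect.

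The article itself shows that practice varies between areas. Medium-risk offenders are eligible only in some areas, and risk grading rests partly on professional judgement.

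The matched cohort is the first quantitative aim. It also supplies the matched controls for the cost-benefit analysis, so the same bias would enter the cost per reoffence avoided. Strengths and limitations does not mention it.

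Timing is a second, smaller problem. An area not delivering CARA at one moment may start within a comparator's 12 months of follow-up. Nothing in the comparator definition aligns the calendar periods of the two groups.

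**Working it through.** The article states no sample size, effect size, reoffending rate or between-force variation for this analysis, so there is no figure of its own to reproduce.

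**Step 1: can force and CARA be separated?** Take 9 CARA forces (the number listed in the article) and m non-CARA forces (assumed). Give each force an indicator and add a CARA indicator. The CARA column equals the sum of the nine CARA-force columns, so the rank is always one short.

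| m | columns (9 + m + 1) | rank |
|---|---|---|
| 1 | 11 | 10 |
| 3 | 13 | 12 |
| 9 | 19 | 18 |

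The result does not depend on there being nine forces. A force fixed effect can never be estimated alongside CARA under this comparator definition. Matching on offender covariates leaves this unchanged, because two matched offenders always come from forces of different type.

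**Step 2: size of the bias (assumed inputs).** Suppose the effect is expressed as a rate ratio, and CARA forces record a fraction r of the events that comparator forces would record for the same behaviour. Then

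expected rate ratio = true rate ratio × r.

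- No CARA effect, r = 0.90: 1.00 × 0.90 = 0.90.
- No CARA effect, r = 0.80: 1.00 × 0.80 = 0.80.
- The bias can run the other way. A true ratio of 0.90 with r = 1.10 gives 0.90 × 1.10 = 0.99, and the effect disappears.

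**Step 3: does a larger study help?** Assume 0.25 events per person-year, one year of follow-up, n matched per arm, simple Poisson variance and no CARA effect. The standard error of the log rate ratio is √[1/(0.25n) + 1/(0.25nr)], and the chance of a significant result in CARA's favour is Φ(|ln r|/SE − 1.96).

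For n = 1000 and r = 0.90: SE = √(1/250 + 1/225) = 0.092, |ln 0.90| = 0.105, and Φ(1.15 − 1.96) = 0.21.

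| n per arm | r = 0.90 | r = 0.80 |
|---|---|---|
| 500 | 0.13 | 0.38 |
| 1000 | 0.21 | 0.65 |
| 2000 | 0.37 | 0.91 |

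The bias does not shrink with sample size, so a larger study makes a false finding more likely.

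**Step 4: the two control definitions.** The matched cohort asks that an area is not delivering CARA now. The controlled time series asks that CARA was not delivered at any time in the study period. Only the second keeps follow-up free of CARA, provided the study period covers it.

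**The case against.** Five points can be made for the plan.

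- **Out-of-area comparators have a rationale.** They avoid selection within a force by who is offered or accepts CARA. That is a real advantage, but it exchanges one source of confounding for another that the article does not address.
- **The covariate list is open.** Its wording does not exclude area-level variables, so it would be too strong to say that all matching is at offender level. What stands is that none of the variables named describes force practice, and that a force fixed effect is not available.
- **The controlled time series removes stable force differences** by contrasting change over time. It does, but it is conditional on feasibility and answers the separate population-level question. The matched cohort has no such step.
- **Earlier comparators from the same forces are not free of problems.** They bring calendar-time confounding, including the COVID-19 lockdowns that the article names, and need person-level records that the monthly aggregates do not provide. This is why they belong in a sensitivity analysis.
- **Naming comparator forces is detail that an article may leave to the full protocol.** This is accepted, and their absence is not the finding.

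A reader might go further and infer that no comparators can exist, because nine forces supply data and nine named forces all deliver CARA. The article never says that these are the same nine. The list sits in the qualitative recruitment section, and non-CARA areas are foreseen both for interviews and for the controlled time series. A reader might also infer that standard errors will be too small because clustering is ignored. No variance method is stated for the matched cohort, and that choice may properly sit in an analysis plan.

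**Conclusion.** The concern holds as a matter of design. As written, the matched comparison is a comparison between two sets of forces, on an outcome those forces generate, with no named adjustment for how they differ. This follows from the two group definitions alone and would remain true however many non-CARA forces were added.

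The size cannot be computed from the article. The range of 0.90 to 0.80 with no CARA effect rests on an assumed 10% to 20% shortfall in recording, and the direction is unknown. The probabilities in the working also rest on an assumed event rate, sample size and Poisson variance. They show how the bias behaves and do not forecast it.

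The wording on timing is a looseness. The two control definitions belong to different analyses and do not contradict each other, and nothing in the article says that a comparator force will start CARA during follow-up. The match between the nine-force ceiling and the nine CARA areas is an inference that the authors should resolve. It is not proof that comparator data are lacking.

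**What to change.** 1. Define comparators as eligible offenders in forces that delivered no CARA from the index date to 12 months after it, in line with the controlled time series.
2. Match on index calendar quarter.
3. Adjust the matched comparison for each force's pre-CARA DVA arrest or recorded-crime rate. Use the monthly series already planned for the time series, and the same series over the same calendar period from control forces. This is a measured force-level covariate, so unlike a force fixed effect it can be fitted alongside CARA. Where person-level records from before roll-out can be obtained, add a matched difference-in-differences analysis as a sensitivity analysis.
4. Base inference on clustering by force, with a correction for the small number of forces.
5. State where comparator data come from and reconcile this with the figure of up to nine forces.

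Items 1, 2 and 5 are changes of wording. Item 3 needs some extra force-level data from control forces. The difference-in-differences analysis needs an additional person-level extract and a parallel-trends assumption that COVID-19 puts under strain. Intervals will be wider, and adjusting for a baseline rate reduces confounding by force without guaranteeing its removal, so the limitation should also be stated.
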